## Abstract

**Background:**

Many preterm infants require supplemental oxygen in the newborn period but experience frequent fluctuations of their oxygen saturation levels. Intermittent episodes of hypoxia or hyperoxia increase the risk of complications. Compliance with achievement of oxygen saturation targets is variable, and the need for frequent adjustments of the inspired oxygen concentration increases workload.

Closed-loop automated oxygen control systems (CLAC) improve achievement of oxygen saturation targets and reduce both episodes of hypoxia and hyperoxia and the number of manual adjustments. This study investigates whether CLAC compared with manual oxygen control reduces the duration of mechanical ventilation in preterm infants born at less than 31 weeks of gestation.

**Methods:**

This randomised controlled trial performed at a single tertiary neonatal unit is recruiting 70 infants born at less than 31 weeks of gestational age and within 48 h of initiation of mechanical ventilation. Infants are randomised to CLAC or manual oxygen control from recruitment until successful extubation. The primary outcome is the duration of mechanical ventilation, and secondary outcomes are the percentage of time spent within target oxygen saturation ranges, the time spent in hypoxia or hyperoxia, the number of manual adjustments required, the number of days on oxygen, the incidence of bronchopulmonary dysplasia and the length and cost of neonatal unit stay. The study is performed following informed parental consent and was approved by the Yorkshire and the Humber-Sheffield Research Ethics Committee (protocol version 1.1, 13 July 2021).

**Discussion:**

This trial will investigate the effect of CLAC on the duration of mechanical ventilation, which is an important clinical outcome as prolonged mechanical ventilation is associated with important adverse outcomes, such as bronchopulmonary dysplasia.

**Trial registration:**

ClinicalTrials.Gov NCT05030337. Registered on 17 August 2021

**Supplementary Information:**

The online version contains supplementary material available at 10.1186/s13063-022-06222-y.

## Trial registration dataset

**Table Tabb:** 

Primary registry and trial identifying number	ClinicalTrials.Gov, NCT05030337
Date of registration	17/08/2021
IRAS no	297749
Source of monetary or material support	King’s College Hospital (KCH)/King’s College London (KCL)
Follow-up duration (if applicable)	Participants will be followed up until their discharge from the neonatal unit
Contact for public/scientific queries	[name] Neonatal Intensive Care Unit King’s College Hospital, [name] [name] [contact]
Public title	Optimising ventilation in preterms with closed-loop oxygen control
Scientific title	Does closed-loop automated oxygen control reduce the duration of mechanical ventilation? A randomised controlled trial in ventilated preterm infants
Country of recruitment	United Kingdom
Health condition(s) or problem(s) studied	Prematurity, mechanical ventilation, hypoxia, hyperoxia
Interventions	Closed-loop automated oxygen control (intervention group)
	Manual oxygen control (control group)
Key inclusion/exclusion criteria:	Inclusion criteria: preterm infants < 31 weeks gestation within 48 h of initiation of mechanical ventilation
	Exclusion criteria: infants > 31 weeks gestation or with major congenital anomalies
Study type	Randomised controlled trial
Date of first enrolment	05/09/2021
Target sample size	70
Recruitment status	Recruiting
Primary outcome	Duration of mechanical ventilation
Key secondary outcomes	Percentage of time spent in target saturation range, time spent in hypoxia and hyperoxia, number of manual adjustments required, number of days on oxygen, diagnosis of BPD, length and cost of neonatal stay

## Role of study sponsor and funder

King’s College London will take primary responsibility for ensuring the study design meets appropriate standards and uses proper conduct and reporting. King’s College London also provides insurance cover to provide for payment of damages or compensation in respect of any claim made by a research subject for bodily injury arising out of participation in a clinical trial or healthy volunteer study with certain restrictions.

King’s College Hospital takes responsibility for arranging the initiation and management of the research and will ensure that appropriate standards, conduct and reporting are adhered to with regards to its facilities and staff involved with the study. King’s College Hospital will also undertake the governance review for the project and provide cover for clinical negligence by any of its staff undertaking the research.

## Roles and responsibilities of study management committees, groups, and individuals

There are no committees or steering groups involved in the management of this study, but all the neonatal consultants have oversight of the study. The chief investigator and sponsor will monitor and audit the conduct of this research and will ensure that appropriate standards and reporting are adhered to (p6, 59–60). All the neonatal consultants have oversight of the study (p6, 70–71). In addition to this, an independent researcher not involved in the project will review trial data upon recruiting half of planned patients. The researcher will evaluate differences in the primary outcome to decide whether enough data have been gained at that point. The research team will remain blinded to the results of the interim analysis unless there are any significant findings (p12, 204–208). This is a non-blinded, randomised, superiority trial.

## Background

Seven to eight per cent of all infants are born prematurely [1] and many require respiratory support in the newborn period [2]. Although such support can be life-saving, preterm infants who require mechanical ventilation and oxygen therapy frequently develop complications [3]. The most common adverse outcome is bronchopulmonary dysplasia (BPD), and importantly prematurely born infants can suffer chronic respiratory morbidity including troublesome respiratory symptoms, lung function abnormalities and exercise intolerance even in adolescence and adulthood [4]. Other complications include intracerebral haemorrhage which can result in cerebral palsy [5] and retinopathy of prematurity (ROP) which can cause blindness [6].

Ventilated neonates frequently require supplemental oxygen, but its use must be carefully monitored due to associated complications. Hyperoxia leads to the development of reactive oxide species (ROS) and increases the risk of bronchopulmonary dysplasia and retinopathy of prematurity [7, 8]. On the other hand, hypoxia increases morbidity and mortality [9, 10]. Therefore, oxygen saturation levels (SpO_2_) are continuously monitored in clinical practice and used to guide adjustments to the inspired oxygen concentration (FiO_2_), which are traditionally made manually by neonatal practitioners. Maintaining oxygen saturations in the target range can be difficult as preterm neonates experience frequent fluctuations with as many as 600 intermittent hypoxic episodes in a week documented in one study [11]. Moreover, prolonged hypoxemic episodes have been associated with increased risk of death after 36 weeks’ postmenstrual age or disability at 18 months corrected age including motor impairment, cognitive or language delay, severe hearing loss or bilateral blindness [12]. Compliance with achievement of SpO_2_ targets is variable within the same patient over time, as well as between patients and centres [13]. Furthermore, target achievement decreases as the number of patients per nurse increases [14].

Closed-loop automated oxygen control (CLAC) systems monitor SpO_2_ values in real-time to calculate and make an adjustment to the FiO_2_ patient delivery without any human intervention [15]. These systems may provide a solution for the low compliance with achievement of target oxygen levels and reduce the need for manual adjustments and hence the workload, as well as reducing complications. Several algorithms exist to calculate the FiO_2_ adjustment in relationship to the SpO_2_ changes in infants with different severities of respiratory disease [16]. An example is the Oxygenie Auto-O_2_ software (SLE) that uses a proportional-integral-derivative control algorithm, and it has been shown to be effective in improving compliance with target achievement in preterm infants, reducing episodes of hypoxia or hyperoxia and the need for manual adjustments to supplementary oxygen [17]. In a randomised crossover study, using that device we demonstrated that preterm ventilated infants experienced fewer prolonged desaturations during the closed-loop automated oxygen control period and spent an increased percentage of time within their target SpO_2_ range with fewer manual adjustments to the inspired oxygen concentration [18]. A review of 16 studies highlighted that the studies of CLAC were very heterogenous for design, population size and device used [15]. Moreover, the majority of those studies had a crossover design and limited data available for analysis. Two reviews emphasised that none of the previous studies had demonstrated whether the clinical outcomes of preterm infants were improved [15, 19]. A subsequent literature review including 18 studies [19] highlighted that CLAC was consistently associated with an increased percentage of time spent within the target oxygen saturation range with fewer manual adjustments to the FiO_2_ and was effective in infants on non-invasive respiratory support or mechanically ventilated at a range of postnatal ages. The results appear to be consistent for all the control algorithms [19] and across different SpO_2_ target ranges [20, 21]. In addition, previous studies demonstrated that CLAC could facilitate earlier weaning of the inspired oxygen concentration when compared to manual control [22, 23], which is a major determinant of an infant’s readiness for extubation. It is, therefore, possible and our hypothesis that use of CLAC would reduce the duration of mechanical ventilation

The aim of this study is to explore if in prematurely born ventilated infants, the use of closed loop automated oxygen control compared to standard care reduced the duration of mechanical ventilation. That is an important clinical outcome as prolonged mechanical ventilation increases the risk of BPD and log-term comorbidities [24]. Our primary outcome is the duration of mechanical ventilation. Secondary outcomes are the percentage of time spent within target oxygen saturation ranges, the time spent in hypoxia or hyperoxia, the number of manual adjustments required by clinical staff, a diagnosis of BPD at 36 weeks post menstrual age and the length of intensive care stay.

## Methods

This is a non-blinded, randomised controlled trial. Infants are allocated to parallel groups in a 1:1 ratio.

### Setting

The setting is a single tertiary neonatal unit at the King’s College Hospital NHS Foundation Trust, London, UK. The unit has previous experience on the use of closed-loop automated oxygen control in the context of trials.

### Inclusion criteria

Inclusion criteria are as follows:
Infants delivered at less than 31 weeks of gestational age requiring mechanical ventilationRecruitment within 48 h of initiation of mechanical ventilation

### Exclusion criteria

Infants delivered above 31 weeks of gestational ageInfants with major congenital abnormalities

### Recruitment

Parents or legal guardians of all eligible infants are initially approached by the clinical team taking care of the infant and if they agree, by a researcher, within 24 h of initiation of mechanical ventilation. The parents are provided with an information sheet about the study. The researchers answer questions and respond to any concerns in a face-to-face meeting and obtain written informed consent. The study was approved by the Health Research Authority and by the Yorkshire and the Humber-Sheffield NHS Research Ethics Committee.

### Randomisation

The randomisation sequence is generated by using an online randomisation generator and concealed in sealed opaque envelopes. This is done by a person independent of the research team who is not involved in the study.

### Enrolment

Infants will be enrolled in the study by the research team within 48 h of initiation of mechanical ventilation following parental consent (supplied as attachment). Infants are randomised to one of the study arms by opening the next envelope.

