### Sample size

In a cohort of 368 preterm infants born between 24 to 30 weeks of gestation, the standard deviation for the duration of mechanical ventilation was 3.83 days [27]. The median duration of ventilation in our NICU was 12 days (mean 19 days). Randomisation of 70 infants allows us to detect a decrease in the duration of mechanical ventilation of three days with a 90% power at the 5% significance level.

At the request of the ethics committee, an interim analysis will be carried out after half the sample has been recruited to review if enough data have been gained at that point. The analysis will be performed by an independent researcher not involved in the project to avoid introducing bias to our data. The research team will be blinded to the results of the interim analysis unless there are any significant findings.

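### The plan as described uses gestational age neither at allocation nor in the primary comparison; the test stays valid, but power is lost if gestational age predicts ventilation days

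*Protocol article*

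**What the plan says.** All references are to the protocol article.

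- **Methods (opening):** "Infants are allocated to parallel groups in a 1:1 ratio".
- **Randomisation:** "The randomisation sequence is generated by using an online randomisation generator and concealed in sealed opaque envelopes". An independent person does this. No stratification factor, block size or minimisation is named.
- **Enrolment:** "Infants are randomised to one of the study arms by opening the next envelope".
- **Inclusion criteria:** any gestation below 31 weeks, with no lower limit.
- **Data collection:** gestational age at birth is among the recorded baseline items.
- **Statistical analysis:** a t test for normally distributed data and a Mann-Whitney test for skewed data, by intention to treat. No covariate or stratum is mentioned.
- **Sample size:** the design SD is given as "the standard deviation for the duration of mechanical ventilation was 3.83 days". The target is set out as "Randomisation of 70 infants allows us to detect a decrease in the duration of mechanical ventilation of three days". Power is put at 90% and the test level at 5%. The same section gives the unit's own median (12 days) and mean (19 days), and says that "an interim analysis will be carried out after half the sample has been recruited". According to the section on roles and responsibilities, that look evaluates differences in the primary outcome.

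**The concern.** Very immature infants and 30-week infants enter through the same sequence, and the stated tests compare the arms as if all infants were exchangeable. If gestational age predicts days on the ventilator, the spread that it causes stays in the error term. The trial then needs a larger true effect to reach significance than it would if this recorded variable were used.

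A chance imbalance in gestational age would also go straight into the observed difference, with nothing in the stated analysis to take it out. Imbalance is larger in smaller samples, so the half-way comparison is the most exposed. At stake is information that a 70-infant, single-centre trial already collects and would leave unused.

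**Working it through.** **1. The plan's own figure.** For a difference of 3 days, SD 3.83, two-sided 5% and 90% power: n per arm = 2 × [(1.960 + 1.282) × 3.83 / 3]² ≈ 34.3, rounded up to 35. The total of 70 is reproduced (power 90.6% by normal approximation, 89.8% by the t distribution).

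**2. Validity.** Type I error was simulated with log-normal outcomes (median 12, mean 19), with gestational age explaining from none to about a third of the variance. It was 3.7-4.4% for the t test and 4.2-5.7% for the Mann-Whitney test, at 35 and 17 per arm. The unadjusted tests keep their level.

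**3. Imbalance on the plan's SD.** The SD of the part of the difference due to gestational age is SD × √R² × √(2/n), where R² is the share of variance explained. The documents do not give R²; 0.1-0.5 is assumed.
- 35 per arm: 3.83 × √0.1 × √(2/35) = 0.29 days, rising to 0.65 days at R² = 0.5.
- 17 per arm: 0.42 to 0.93 days.
- Even at R² = 1, a shift of 3 days or more has probability 0.1% at 35 per arm and 2.2% at 17.

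**4. Imbalance on the unit's own durations.** Mean and median cannot differ by more than one SD, so the SD is at least 19 − 12 = 7 days. If durations are log-normal (an assumption), σ = √(2 ln(19/12)) = 0.959 and SD = 19 × √(exp(0.959²) − 1) = 23.3 days.
- SD 7, R² 0.3: probability of a shift of 3 days or more is 0.1% at 35 per arm and 2.3% at 17.
- SD 15, R² 0.3: 13% and 29%.
- SD 23.3, R² 0.3: 33% and 49%.
- Log-normal simulation with two equal gestational-age strata explaining 10-50% of log-variance: 2-28% at 35 per arm. This is lower than the normal formula at SD 23.3 (9-45% over the same R² range) because the strata act on log duration.

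**5. What using gestational age gains.** On the log scale, with 35% explained, the SD of the estimated difference is 0.229 unadjusted and 0.186 adjusted, both under unstratified allocation. The variance ratio is (0.186/0.229)² = 0.66, so the unadjusted comparison of 70 infants carries the information of about 0.66 × 70 ≈ 46 infants analysed with adjustment. With stratified allocation as well, the adjusted SD is 0.182, which is almost the same.

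Simulated power for a 40% reduction in duration (log-normal, median 12, mean 19, two equal strata, 35 per arm, unstratified allocation):

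| Log-variance explained | Mann-Whitney | Stratified rank test |
|---|---|---|
| 20% | about 55% | 65% |
| 35% | about 55% | 74% |
| 50% | about 55% | 85% |

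Stratifying the allocation as well adds 1-3 percentage points. The 40% reduction was chosen to compare the analyses. It is larger than the plan's 3 days, which is 3/12 = 25% of the unit's median.

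**6. The plan's 3-day target.** With SD 3.83 and R² 0.1-0.5, adjustment raises power at 70 infants from 90.6% to 93.2-99.6%. With SD 23.3 it raises power only from 7.8% to 8.2-11.5%.

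**The case against.** - **The absence of strata is partly inferred.** The article condenses a fuller protocol, and the next envelope could mean the next one in the infant's stratum. This stands as a limit. The article nevertheless describes a single sequence, and it commits to specific two-sample tests, so the point about the analysis does not rest on silence alone.
- **Unstratified randomisation with an unadjusted test is legitimate.** This stands. A reader might infer that chance imbalance could mimic or hide the 3-day effect, so that the result could not be trusted. The documents do not support that. The test level already allows for chance imbalance. On the stated SD of 3.83 days, or on the minimum of 7 days implied by the unit's figures with 30% explained, a 3-day shift at 35 per arm is very unlikely. It becomes common only with an SD well above that minimum (15-23 days) and an assumed prognostic strength.
- **The unit's historical spread may not be that of the outcome.** Trial duration runs from enrolment and, for infants still ventilated after day 28, stops at the first extubation attempt, so its SD may differ from 23 days. This also stands. Durations are not capped at day 28, however, so a long tail remains possible.
- **Re-queuing envelopes would gain little.** This is correct once the analysis is adjusted. Recruitment has already begun, so only later infants could be stratified, and blocks within strata make allocation slightly more predictable in an open-label trial at one unit.

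**Conclusion.** The point holds as one of efficiency. As described, gestational age is used neither at allocation nor in the primary comparison, although it is recorded for every infant. The comparison remains valid at about 5%. If gestational age explains 20-50% of the variance of log duration, a stratified rank test would raise power for a 40% reduction from about 55% to 65-85%, nearly all of it without any change to the envelopes. Imbalance matters most at the half-way look, where its SD is √(35/17) ≈ 1.4 times that at the end.

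The size depends on the log-normal shape, the strength of gestational age as a predictor and equal strata, none of which the documents give. On the plan's SD the imbalance is small. The gap between an SD of 3.83 days and the unit's mean of 19 and median of 12 is a separate and larger problem, which this change does not repair.

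**What to change.** In Statistical analysis, prespecify that the primary comparison takes account of gestational age at birth, at both the interim and the final analysis. Two suitable forms are a rank test stratified by two gestational-age bands (for example below 27 and 27-30 weeks) or a regression of log duration on arm with gestational age as covariate. Choose one form, and its bands if used, before anyone sees outcomes by arm. This covers every infant, including those already randomised, and needs no extra infants or data: the cost is a sentence or two and a minor amendment.

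In Randomisation, state whether allocation is stratified or blocked. If the full protocol does not already stratify, two envelope queues by gestational-age band, with random block sizes not disclosed to the research team, are an option for infants not yet randomised. The cost is a second envelope set and slightly more predictable allocation, for a gain of about 1-3 points of power once the analysis is adjusted.

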### Blinding

The study is not blinded. Decisions regarding ongoing care, for example ventilator settings and interventions such as blood gases and chest radiographs, are made by the clinical team as per the neonatal unit’s guidelines.

### Intervention

At enrolment, participants are randomised to receiving either closed-loop automated oxygen control (intervention group) or manual control of the inspired oxygen concentration. All infants are ventilated using the SLE6000 ventilators and ventilation settings are manually adjusted by the clinical team as per the unit’s protocol. In addition to standard care, infants in the intervention group are connected to the Oxygenie Auto-O_2_ software (SLE). This software uses oxygen saturation levels from the SpO_2_ probe attached to the neonate, which are fed into an algorithm, to automatically adjust the percentage of inspired oxygen to maintain oxygen saturations within the target range. Manual adjustments including the percentage of inspired oxygen are allowed at any point during the study, if deemed appropriate by the clinical team.

The nurse-to-patient ratio is according to the unit protocol that is determined on the patient’s acuity. Respiratory care will be provided for all infants by the clinical team as per the unit’s guidelines. All infants will be ventilated using the SLE6000 ventilators and ventilation settings will be adjusted manually following the unit’s protocol. The intervention will be performed in addition to standard care and manual adjustments will be allowed at any point during the study, if deemed appropriate by the clinical team (p10–11, 173–180).

Infants are studied from enrolment until successful extubation [25]. For infants who fail extubation and require reintubation within 48 h, they continue in their initial study arm if they are less than 28 days old. At KCH NICU, preterm infants with non-chronic respiratory pathology are extubated from a targeted tidal volume of 5 ml/kg, a peak inspiratory pressure at or below 18 cm H_2_O and a backup rate of 40 breaths per minute. FiO_2_ requirement should be less than 0.3. The infant should have good respiratory drive as well as blood gases. Therefore, for infants randomised to the intervention group, closed-loop oxygen delivery resumes. Preterm infants that remain ventilated beyond day 28 of life continue at their study arm (closed-loop automated oxygen control or manual oxygen control) till their first extubation attempt (see Fig. 1).

